## Abstract

**Background:**

Many babies in the UK are born to drug-dependent parents, and dependence on psychoactive drugs during the postnatal period is associated with high rates of child maltreatment, with around a quarter of these children being subject to a child protection plan. Parents who are dependent on psychoactive drugs are at risk of a wide range of parenting problems, and studies have found reduced sensitivity and responsiveness to both the infant’s physical and emotional needs. The poor outcomes that are associated with such drug dependency appear to be linked to the multiple difficulties experienced by such parents.

An increase in understanding about the crucial importance of early relationships for infant well-being has led to a focus on the development and delivery of services that are aimed at supporting parenting and parent–infant interactions. The Parents under Pressure (PuP) programme is aimed at supporting parents who are dependent on psychoactive drugs or alcohol by providing them with methods of managing their emotional regulation, and of supporting their new baby’s development. An evaluation of the PuP programme in Australia with parents on methadone maintenance of children aged 3 to 8 years found significant reductions in child abuse potential, rigid parenting attitudes and child behaviour problems.

**Methods/design:**

The study comprises a multicentre randomised controlled trial using a mixed-methods approach to data collection and analysis in order to identify which families are most able to benefit from this intervention.

The study is being conducted in six family centres across the UK, and targets primary caregivers of children less than 2.5 years of age who are substance dependent. Consenting participants are randomly allocated to either the 20-week PuP programme or to standard care.

The primary outcome is child abuse potential, and secondary outcomes include substance use, parental mental health and emotional regulation, parenting stress, and infant/toddler socio-emotional adjustment scale.

**Discussion:**

This is one the first UK studies to examine the effectiveness of a programme targeting the parenting of substance-dependent parents of infants and toddlers, in terms of its effectiveness in improving the parent–infant relationship and reducing the potential for child abuse.

**Trial registration:**

International Standard Randomised Controlled Trial Number Register: ISRCTN47282925

## Background

Drug and alcohol dependency is a significant public health problem with major human, social and economic consequences. In 2009/10, 8.6% of adults in the UK had used one or more illicit drugs within the last year, and 3.1% of adults had used Class A drugs. These rose to 20% and 7%, respectively, in the 16- to 24-year-old age group. During 2009/10, 206,889 people were in contact with structured drug treatment services (those aged 18 and over) [1].

The evidence suggests that around one-third of drug users in the UK are women, of which as many as 90% are of childbearing age [2]. Estimates also show that around 2% to 3% of children under 16 have a parent who is a problematic drug user and around 1% of births are to drug users and a similar number to problem drinkers [3]. Of children less than 1 year old, it has been estimated that 19,500 live with a parent who has used Class A drugs in the last year and 93,500 live with a parent who is a problem drinker [4].

Drug-dependent parents are at high risk for maltreatment of their children. Around 25% of all children subject to a child protection plan are cared for by a parent with a substance misuse problem [5] and one study found a significantly higher risk of child protection proceedings amongst infants of substance-misusing parents compared with infants of non-drug users (32.4% vs. 7.1%) [6]. These figures are similar for other countries such as the US [7,8] and Australia [9].

The first 2 years of a child’s life are a particularly important developmental phase, primarily because of the impact of early parent–infant interaction on the infant’s developing neurological [10] and attachment systems [11]. Substance-dependent parents demonstrate a range of parenting difficulties and deficits [12], and in particular a reduced capacity for sensitivity and attunement during this important period [13-16].

The poor quality of caregiving is influenced by the problems that co-occur with drug dependence, such as, psychiatric disorders and psychopathology [14], particularly disorders of affect regulation [17]. The infants of drug-dependent parents may also have a range of neurobiological problems as a result of drug exposure *in utero*[18,19] making it difficult to assess whether the compromised interaction is due to the impact on the infant’s neurobehavioural system, the dyadic organisation of the interaction or both [15]. These infants are also often exposed to a range of other substances including psychomotor stimulants such as alcohol and nicotine [20].

The research mentioned above highlights the need for interventions that target the parenting of substance-dependent parents in addition to a focus on drug dependency, and four systematic reviews [21-24] have examined the impact of community-based substance-misuse treatment programs combined with interventions aimed explicitly at improving parenting. These show that studies that have focused explicitly on infants or toddlers are limited and include standard home visiting programmes [25-28], which have on the whole showed limited evidence of effectiveness, and a number of more promising approaches including mentalisation-based programs in community [29,30] and residential settings (not discussed further here) [31,32]. Other promising interventions that have been used with substance-dependent parents of older children include standard parenting skills and case-management approaches [33,34], psychotherapeutic relational therapy groups [35,36], court-based models of working (not discussed further here) [37], and the mindfulness-based programme being trialled here [9].

Focus on Families (FOF) [33] was one of the earliest attempts to combine behavioural family therapy and parenting skills training with home-based case management and clinic-based relapse prevention, to support methadone-maintained parents of children aged 3 to 14 years. This approach achieved significant reductions in parental drug use, and improvements in terms of parental skills, deviant peers and family management (*ibid*), and although there were no between-group differences in substance-use disorders at the 15-year follow-up, males in the FOF group had a significantly lower risk of developing a substance-use disorder compared to those receiving standard care [34].

Another approach that has recently been developed to support methadone-maintained mothers of older children is Relational Psychotherapy Mother’s Groups (RPMGs) [35,36], which comprises a 24-week programme involving a supportive therapist, interpersonal relational focus group treatment and insight-oriented parenting skill facilitation. The focus was on psychological functioning in terms of reducing anger, depression and guilt, in addition to addressing specific parenting issues by encouraging the use of alternatives to physical punishment, alongside age-appropriate discipline and warmth. A randomised controlled trial (RCT) comparing RPMGs with recovery training found that despite initial gains in the post treatment phase in terms of self-reported child maltreatment, cocaine abuse, emotional adjustment and depression [35], these results were not maintained to the 6-month follow-up [36]. The authors suggest that this may have been due to the abrupt cessation of the therapy programme.

The concept of mentalisation refers to the capacity to understand the actions of self and others in terms of intentional states (for example, thoughts, beliefs and desires), and has been proposed to be a key mechanism in improving affect regulation and caregiving competence [38], and may be a significant factor in the functioning of high-risk substance-dependent women [32]. This construct has been incorporated into a number of treatment approaches targeting high-risk mother-infant/toddler dyads including maltreating parents of infants [39], high-risk women of infants where there are issues such as trauma and unresolved loss [40] and substance-dependent parents of toddlers [29]. The Mothers and Toddlers Program (MTP) [29] comprised a 12-session weekly ‘individual parenting therapy’ for mothers with a child under 36 months who were enrolled in outpatient substance-use treatment. The intervention incorporated a range of strategies explicitly focused on enhancing maternal capacity for reflective function and reducing distorted mental representations of parenting. The findings of an RCT [29] comparing MTP with a parent education programme, showed that post treatment, mothers in the MTP group had significantly higher scores for ‘self-focused’ but not ‘child-focused’ reflective functioning, that were maintained to the 6-week follow-up [30]. There were also group differences in caregiving behaviour and child behaviour (that is, increased communication and a delayed effect for the contingency score was found at the follow-up), and in levels of depression and psychiatric distress. Substance use improved across both groups. Group differences in maternal caregiving behaviour were maintained to the follow-up, but not maternal depression, and the results for psychiatric symptoms favoured the Parent Education Programme (PE) group. Maternal representations of the child were significant at the follow-up only [30]. These findings suggest that this intervention has considerable promise in the short term when delivered by highly trained and supported therapists.

Overall, a number of innovative ways of working with substance-dependent parents of infants and toddlers have been developed during the past 10 years. Recognising the importance of helping women who are experiencing a range of problems to manage their roles as mothers has been a central theme. This is a significant challenge for the field, and although promising approaches are emerging, the duration of the programmes and focus on the wider social context in terms of social support have been highlighted as key factors requiring careful consideration. The current study adds to this literature by providing a rigorous evaluation of a programme with demonstrated efficacy [9]. Further, the current evaluation involves the programme being delivered by front-line practitioners engaged in routine clinical practice, many of whom do not have formal qualifications in social work or psychology, thereby comprising a real-world effectiveness study.

### Rationale for the parents under pressure programme

Adverse outcomes for the children of drug-dependent parents, including child maltreatment, are not associated specifically with parental drug use as a single risk factor, but rather with the complex interplay between child functioning, parental drug use, parental psychopathology, parenting practices, family environment (including spousal relationships and the availability of social support) and socioeconomic factors such as unemployment and poverty [41].

The relationship between impulsivity and poor affect regulation has been widely documented in the substance-abuse literature and it is clear that these play a role in the aetiology of substance abuse in addition to having an impact on treatment outcome [42]. The seminal work by Linehan in her development of dialectical behaviour therapy emphasised the importance of addressing dysregulated affect in women with a range of impulse control disorders including substance abuse [43-45]. Notably, this work addressed the problem of dysregulated affect through the explicit incorporation of mindfulness-based approaches that aim to increase capacity for self-regulation of attention in terms of a focus on immediate experience, alongside the adoption of a particular stance with regard to that experience, which is characterised by curiosity, openness and acceptance [46,47]. However, evidence on the effectiveness of approaches that include other components, such as case management [33] and social support [29], suggests that treatment needs to address multiple domains of family functioning.

### Parents under pressure programme

The Parents under Pressure Programme (PuP) was developed as an intensive home-based intervention underpinned by an integrated framework of family functioning [48], which draws strongly on attachment theory with a focus on developing a safe and nurturing relationship. The programme is underpinned by a recognition that the quality of the parent–child relationship is related to the parent’s capacity to provide sensitive, responsive and nurturing caregiving [45], and the parent is helped to recognise their own strengths and potential difficulties using video feedback, shared discussion with the practitioner and completion of exercises using the parent’s workbook. Additionally, difficulties in managing dysregulated affect and impulsive behaviour, both in relation to parenting and to substance abuse, are addressed through the use of mindfulness exercises and a focus on recognising and managing negative emotional states. In relation to the former, these include exercises that involve mindfulness meditations in addition to helping a parent develop a greater awareness of being fully present in the moment with their infant during daily activities (for example, taking pleasure in watching an infant sleep, and during bath time and play). In relation to the latter, the use of techniques such as ‘urge surfing’, understanding cravings and learning to manage negative mood states without the use of substances, complement the care received from the standard drug and alcohol treatment services [46,47].

Evaluation of the programme with parents on methadone maintenance of children aged 3 to 8 years found significant reductions in child abuse potential, rigid parenting attitudes and child behaviour problems [9,49]. There was also a significant reduction in methadone dose, within a treatment context in which methadone doses were largely determined by parental choice. Changes in dose therefore reflected client decision-making rather than treatment policy that was abstinence focused [9].

The PuP programme contains 12 modules and these are delivered across 20 calendar weeks. The selection and delivery of the modules are determined by the assessment. The programme is embedded within a case-management framework, and day-to-day issues such as housing and finance provide a therapeutic opportunity to put coping skills into practice in a mindful and emotionally contained manner. Sessions are conducted in the home and last between 1 and 2 hours with content drawn from the parent’s workbook. Additional case management occurs outside the treatment session, according to individual family needs (for example, housing, legal advice or school intervention).

The programme begins with a comprehensive assessment and individual case formulation conducted collaboratively with the family. Specific targets for change are identified during the assessment, which then become the focus of treatment. Each module comprises a theme that continues throughout treatment. For example, Module 6, *Connecting with Your Baby*, focuses on helping a parent connect with their child through a series of exercises that help the parent reflect on their own relational experience with their baby. There is an emphasis on learning their baby’s language, and ‘mindful play’ in which a parent is taught to use mindfulness constructs to observe, describe and participate during play and special times.

Module 7, *Mindful Child Management*, teaches non-punitive child management techniques and locates these within a developmental context to ensure that parents understand the most age-appropriate strategy to use. This also requires a sensitive understanding of the baby’s or child’s cognitive capacity and developmental charts supplement the parent’s workbook as a way of helping parents feel proud about their baby’s or child’s development while also developing realistic views about their baby’s or child’s capacity. Mindfulness techniques are used to help parents gain greater control over their own emotional responsivity in both stressful parenting situations, such as prolonged crying of an infant, and situations requiring behaviour management in order to reduce impulsive, emotion-driven punishment [50,51].

The use of the modules depends on the personal situation of the parent. For example, the *Relationship* module includes a focus on improving communication in intimate relationships. It also includes sections on defining the qualities of a good and loving intimate relationship for couples with a troubled relationship history.

### Study objective

The objective of this study is to evaluate the effectiveness, cost effectiveness and user acceptability of the Parents under Pressure programme for substance-dependent parents of infants less than 2.5 years of age.

#### *Hypotheses*

The delivery of a 20-week mindfulness based intervention to parents with substance-abuse problems will reduce the potential for child abuse. The programme will also improve parent–infant/toddler interaction, infant/toddler social and emotional adjustment, and parental psychological well-being in terms of stress, depression and anxiety, and the capacity for affect regulation. This will also be manifest in reduced substance use. The impact of the programme on the primary outcome (that is, child abuse potential) will be mediated via the parent’s capacity for affect regulation.

## Methods/design

### Study design

The study comprises a mixed-methods, multicentre randomised controlled trial involving an explanatory sequential design, in which qualitative data will be collected in addition to the quantitative effectiveness and cost-effectiveness data, with the aim of providing further understanding of the data that has been obtained.

### Project timescale

The trial commenced in October 2011 and will end in December 2015. Recruitment of participants will be staggered across the six trial sites.

### Randomisation

Randomisation will be stratified by centre using minimisation [52], and consenting parents will be randomly allocated to one of two arms, using a computer-generated numbers table (using Stata v7) by an independent statistician. The intervention arm will receive the Parents under Pressure programme alongside standard services for substance-dependent parents, and the control arm will receive standard services alone, which will vary by site but will mostly be adult facing and linked to the management of addiction and relapse, alongside the implementation of child protection services as appropriate. Standard services will also provide families with access to universal health and parenting support, children’s centre support and self-help groups in addition to the more targeted support from drug and alcohol treatment services.

To reduce bias and contamination, study staff and researchers involved with delivering the PuP intervention will have no contact with families in the control group. All data will be collected by a researcher who is blind to group allocation (see Data-collection process). Some contamination within centres may still occur, however, because there is a small population of families at each site and families in the intervention group may pass ‘helpful’ information to families in the control group. Furthermore, participants may reveal their treatment allocation to the researcher whilst undergoing data-collection activities, such as the qualitative interviews. An assessment of the extent to which contamination has occurred will be made as part of the process of data collection (for example, recording any unmasking of group allocation during interviews with families and asking if families know others in the study). If levels of contamination are found to be high in either study group, an extra confounder variable denoting contaminated controls will be added to the analysis and the effects of this contamination investigated (see Data analysis section). However, we do not expect that contamination between groups will be a significant issue because the ‘dose’ received by control families will be low compared with that received by the intervention group (that is, the intensive 20-week programme).

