### Data-collection process

Data will be collected by a researcher who is blind to study arm, in the respondent’s home or at a drug treatment centre. Study participants will be requested not to disclose their group allocation to the researcher, and loss of blinding will be recorded and taken into account at the analysis stage. The data will comprise a range of self-report questionnaires that are robust to loss of blinding, and independent observations of the parent and infant, which will be rated externally to the research team. The researcher will provide assistance with the completion of self-report questionnaires where this is required. Data will be collected at baseline, immediately post-intervention and at the 6-month follow-up.

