### Data analysis

All data will be analysed using an intent-to-treat analysis, unless significant deviations from the intended treatment arm are detected, in which case a per protocol analysis may also be conducted. Descriptive statistical summaries (for example, medians and ranges, means and variances, or contingency tables, depending on the variable distribution and type) will be presented for the primary and secondary outcome measures at each time point. Baseline data will be scrutinised to check comparability between treatment arms and to highlight any characteristic differences between the six trial recruitment sites. Any disparities found will be added to subsequent models to compensate for these differences.

Data collected from families who were approached but refused to take part and those who dropped out will also be analysed and examined for trends (using only basic information such as consenting participant age, gender and intervention arm), alongside qualitative data concerning the reasons for dropping out. We will also investigate potential contamination between intervention groups, as described in the Randomisation section above.

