#### *Primary analysis*

Changes in the CAPI score between baseline and at the 6-month follow-up will be compared for the intervention groups using ANCOVA with the site where the family was recruited used as an independent confounder.

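### The planned contaminated-controls variable is a post-randomisation, control-only indicator, not a confounder; a model containing it no longer estimates the intent-to-treat contrast, and the protocol does not say it stays out of the primary ANCOVA

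*Protocol article*

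**What the plan says.** The Randomisation section expects that "families in the intervention group may pass ‘helpful’ information to families in the control group". It plans to assess contamination during data collection, for example by "recording any unmasking of group allocation during interviews with families and asking if families know others in the study". The rule that follows has a condition, "If levels of contamination are found to be high in either study group", and a consequence: "an extra confounder variable denoting contaminated controls will be added to the analysis and the effects of this contamination investigated". The section adds that contamination is not expected to matter much, because controls would receive little of the programme.

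The Data analysis section sets the principle: "All data will be analysed using an intent-to-treat analysis, unless significant deviations from the intended treatment arm are detected". It then refers back: "We will also investigate potential contamination between intervention groups, as described in the Randomisation section above". The Primary analysis section describes changes in the abuse-potential score from baseline to 6 months, "compared for the intervention groups using ANCOVA with the site where the family was recruited used as an independent confounder". It names no contamination term. Separately, the Data-collection process section says that "loss of blinding will be recorded and taken into account at the analysis stage", without naming a method.

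**The concern.** A confounder of a randomised comparison would have to precede allocation. Contamination follows it and, as the variable is defined, exists in one arm only. Adjusting for it does not remove a baseline imbalance. It takes the flagged controls out of the treatment contrast, while families of the same kind remain in the PuP arm.

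The flags proposed as examples are knowing other trial families and unmasking at interview. These record acquaintance and disclosure, not receipt of PuP content. They may well go with social connectedness or engagement, so it cannot be presumed that flagged controls have average prognosis.

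If the adjusted model became the main result, the trial would report something other than the intent-to-treat effect it promises. The direction of the shift would depend on who happened to be flagged. The rule is also internally uneven: its trigger refers to either group, but the variable describes controls only.

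**Working it through.** The protocol gives no figure on this point, so there is none to reproduce. The check is algebra, then a simulation.

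**Inputs from the protocol.** A control-only indicator (Randomisation); an ANCOVA with site as the only named covariate (Primary analysis); 57 per arm and a target effect of 0.5 SD (Sample size).

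**Assumed, because the protocol gives no values.** The share flagged p; the prognostic gap g between flagging-prone and other families that baseline adjustment does not remove; the effect c of contamination on a control's outcome; a baseline-to-follow-up correlation of 0.5. Lower scores are better, so a benefit is negative.

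**Step 1: what the coefficient estimates.** Let T = 1 for PuP and D = 1 for a flagged control. D is 0 for every PuP family. T and D together define three groups (PuP, unflagged controls, flagged controls) and the model gives each its own mean. The coefficient of T is therefore mean(PuP) − mean(unflagged controls). With site or baseline added it is the covariate-adjusted form of the same contrast.

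**Step 2: distance from intent-to-treat.** Set the mean of families not prone to flagging to 0 under control. Randomisation puts the same share p of prone families in each arm. With a common treatment effect τ:

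- PuP mean = τ + pg
- All-control mean = p(g + c)
- Intent-to-treat estimate = τ + pg − p(g + c) = τ − pc
- Estimate with the indicator = τ + pg − 0 = τ + pg
- Shift = (τ + pg) − (τ − pc) = p(g + c)

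**Step 3: numbers with c = 0 and a residual gap of 0.5 SD.** The shift is 0.1 × 0.5 = 0.05, 0.2 × 0.5 = 0.10, 0.3 × 0.5 = 0.15 and 0.4 × 0.5 = 0.20 SD. That is 10% to 40% of the 0.5 target, in either direction according to the sign of g.

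**Step 4: simulation** (57 per arm, ANCOVA with a baseline covariate, 4,000 runs per scenario, two-sided 0.05, gap not visible at baseline, c = 0):

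| True effect | p | g | Intent-to-treat estimate (rejection) | Estimate with indicator (rejection) |
|---|---|---|---|---|
| 0 | 0.2 | −0.5 | 0.001 (5.6%) | −0.097 (9.0%) |
| 0 | 0.2 | +0.5 | −0.001 (5.1%) | 0.100 (9.5%) |
| 0 | 0.4 | −0.5 | −0.001 (4.6%) | −0.199 (17.2%) |
| 0 | 0.4 | +0.5 | −0.001 (5.1%) | 0.199 (17.5%) |
| −0.5 | 0.4 | −0.5 | −0.504 (84.5%) | −0.701 (95.2%) |
| −0.5 | 0.4 | +0.5 | −0.496 (84.1%) | −0.300 (33.3%) |
| −0.5 | 0.4 | 0 | −0.500 (85.8%) | −0.500 (75.0%) |

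The estimates agree with Step 2. The last row shows no bias when g and c are both 0, only lost precision.

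**Step 5: gap already present at baseline.** If prone families differ by 0.5 SD at baseline and again at follow-up, baseline adjustment with correlation r leaves g = (1 − r) × 0.5. At r = 0.5 this is 0.25, and for p = 0.1 to 0.4 the shift falls to 0.025 to 0.10 SD. It is smaller for larger r and larger for smaller r. For a plain change score the residual gap is 0.5 − 0.5 = 0, and so is the shift. A simulation at 54 per arm with p = 0.3 and no true effect gave 0.073 (formula: 0.3 × 0.25 = 0.075) with 6.8% rejection under baseline adjustment, and 0.000 with 5.4% for the change score.

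**Step 6: contamination that really dilutes.** With g = 0, c = −0.2, p = 0.4 and τ = −0.5, intent-to-treat targets −0.5 + 0.4 × 0.2 = −0.42 and the indicator model targets −0.50. The simulation gave −0.418 and −0.498.

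**The case against.** The strongest reply is that the model may never touch the primary result. The Primary analysis section names site and nothing about contamination. The Data analysis section commits to intent-to-treat and then says contamination will also be investigated. The Subsidiary analyses section is where further work on confounding variables is placed. On that reading the indicator belongs to an exploratory model beside the intent-to-treat result. This is reasonable, but the text does not fix it: the rule says the variable is added to the analysis, and no sensitivity label is attached, although the Subsidiary analyses section uses that label for multiple imputation. A reader might infer that following the protocol necessarily contradicts intent-to-treat or biases the primary estimate. The documents do not support that.

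Second, bias is not automatic. Step 6 shows that when flagging is unrelated to prognosis, the indicator model validly estimates the effect against uncontaminated controls. That stands, but it is a different target from intent-to-treat. The protocol's own expectation of little exposure among controls suggests a small c, which leaves selection as the main part of any shift.

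Third, the size rests wholly on assumed values and shrinks when the gap is already visible at baseline (Step 5). That stands too. The larger figures need a gap that baseline scores do not capture.

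Fourth, a reader might infer that loss of blinding will also be entered as a covariate. The Data-collection process section says only that it will be taken into account. Reporting rates by arm would satisfy that sentence, so no bias from an unblinding covariate can be charged to this plan. Finally, the missing threshold for high contamination is ordinary analysis-plan detail and is not counted here.

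**Conclusion.** The point holds for the contamination rule. The variable is wrongly called a confounder, and any model containing it targets PuP against uncontaminated controls rather than the randomised comparison. Whether this affects the primary result depends on a choice the protocol leaves open.

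If the indicator did enter the main model, the estimate would move by p(g + c): 0.05 to 0.20 SD for p of 0.1 to 0.4 with an assumed residual gap of 0.5 SD and c = 0. With no true effect, simulated type I error was 9.0% to 9.5% at p = 0.2 and 17.2% to 17.5% at p = 0.4. The shift is about half as large if the gap is present at baseline and adjusted for at a correlation of 0.5. It is nil if flagging is unrelated to prognosis and has no effect on outcome, or if g and c cancel. All of these inputs are assumptions. The sentence on loss of blinding needs clarification at most.

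**What to change.** In the Randomisation section, replace the rule and drop the word confounder. State that the primary ANCOVA remains intent-to-treat, includes all controls and does not contain the contamination variable. State that contamination will be reported by arm. Label any contamination model as a sensitivity analysis whose target is not the intent-to-treat effect.

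If controls' actual receipt of PuP content is measured, a method that respects randomisation is preferable, such as a complier-average (instrumental-variable) analysis. Knowing other families or disclosing allocation is not a measure of exposure and would not support it.

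In the Data-collection process section, add that the primary model is not adjusted for loss of blinding.

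The cost is two reworded sentences and, if contamination turns out to be material, one supplementary analysis; the complier-average version also needs receipt of PuP content to be recorded for controls. The price in interpretation is that the intent-to-treat estimate may be diluted if contamination is real, which the sensitivity analysis can then address openly.
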